### **3.6.4 Immunology Laboratory Evaluations**

There are two different parts to the immunogenicity evaluations that will be conducted as part of this clinical trial, which are described below:

1. Real-time evaluation of vaccine immunogenicity in a sample of subjects from each clinical trial site
2. Sample storage until the end of the trial to allow the detection of potential immunological correlates of protection.

#### **3.6.4.1 Real Time Evaluation of Vaccine Immunogenicity**

There are three assays which will be used to determine vaccine immunogenicity on the first 5% of the subjects enrolled (a total of 70 subjects, across ART+/ART- strata as defined in Section 3.3, with a minimum of 30 subjects at each clinical site). Samples will be obtained from these 70 subjects prior to each vaccination, and at 7 and 28 days after each vaccination. All evaluations will be performed by technicians blinded to treatment group.

1. Ex-vivo IFN- $\gamma$  ELISPOT assays will be conducted at all clinical trial sites on fresh PBMC.
2. Whole blood from all 70 subjects collected only prior to each vaccination and 7 days after each vaccination will be frozen for use in the WB ICS assay, which will be performed centrally.
3. [name]'s laboratory at the Pasteur Institute, Brussels, will analyze the Ag85A specific antibody response on frozen plasma or serum samples collected from vaccinees before and after MVA85A/AERAS-485 administration. Recombinant histidine-tagged Ag85A from *M. tuberculosis* (identical to Ag85A of *M. bovis* BCG) will be prepared using affinity chromatography on Ni-columns. In parallel, native Ag85A will be purified from *M. bovis* BCG culture filtrate by sequential chromatography on Phenyl-Sepharose, DEAE sephacel and molecular sieving. Sera will be analyzed for presence of Ag85A specific IgG antibodies by ELISA. A selected number of serum samples will also be analyzed for the presence of specific antibodies against Ag85A from *M. avium* as a read-out for pre-existing immunity against environmental mycobacteria. Western blot analysis against culture filtrate of BCG will also be performed on this group of serum samples.

Any residual PBMC, WB ICS samples and plasma from these 70 subjects will be stored for cryopreservation as described in 3.6.4.2 below wherever possible.

**Table 3 Summary of Real Time Immunology Evaluations**

| Sample type                      | Assay                                 | Purpose of Assay                                            | Study Days                                                                                                                          |
|----------------------------------|---------------------------------------|-------------------------------------------------------------|-------------------------------------------------------------------------------------------------------------------------------------|
| Immunology
(whole blood/PBMC) | Intracellular cytokine staining (ICS) | Determine cellular immune response to study vaccine         | Prior to each vaccination, and at 7 and 28 days after each vaccination. (PBMC and ELISPOT only at 28 days post-vaccination.) |
|                                  | Cytokine ELISPOT                      |                                                             |                                                                                                                                     |
| Immunology
(serum/plasma)     | Ag85A antibody response               | Exploratory measurement of immune response to study vaccine | Prior to each vaccination, and at 7 and 28 days after each vaccination.                                                      |

### 3.6.4.2 Immune Correlate Samples

Two different samples will be collected on the specified study days (Tables 3-1 and 3-2) and stored for all subjects randomized (except for the 70 participants mentioned above):

1. PBMC sample
2. Serum/plasma sample

When the trial is completed and unblinded, TB cases and matched controls will be identified and selected immunological analyses will be conducted. Such analyses, to be conducted at Oxford University, Aeras, and the clinical trial sites, may include polychromatic flow cytometry to determine the functionality and phenotype of the antigen specific T cells, CFSE proliferative assays, microarray and RT-PCR analysis. Other exploratory immunological assays may also be conducted to fully characterize the vaccine induced immune response.

A summary of immunologic assays to be performed on blood specimens is shown in Table 3-2. Staff at the clinical research site will refer to the most current version of the Specimen Management Manual (provided under separate cover) for further instructions and additional information on specimen collection and processing.

### 3.6.5 Concomitant Medications

The collection of information on concomitant medications used by subjects following vaccination will coincide with the collection period of adverse events. The collection period for concomitant medications associated with the treatment of adverse events will be 28 days following each vaccination. The collection period for concomitant medications associated with the treatment of serious adverse events (SAE) and anti-retrovirals for the treatment of HIV will be Study Day 0 through the end of the study.

Concomitant medication includes prescription and non-prescription drugs or other treatments, and any vaccines other than the study vaccines. The name of the medication, treatment start and stop dates (or ‘ongoing’), route of administration, and indication must be recorded on the

Concomitant Medications electronic case report form (eCRF). The indication recorded on the Concomitant Medications eCRF must correspond to a medical term/diagnosis recorded on the adverse event (AE) eCRF, or to a pre-existing condition noted in the subject's medical history, or be noted as prophylaxis, e.g., dietary supplement.

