### **3.6.6 Subject Follow-up and Contact**

All subjects who are assigned a subject identification number and receive study vaccine will be followed according to the protocol unless consent is withdrawn.

Subjects will be instructed to contact a study team member to report new diagnoses or new or worsening adverse events and to come to the study clinic if medical attention is needed, provided the urgency of the situation permits. For emergencies and other unscheduled visits to a medical facility other than the study clinic, medical records will, to the extent possible, be obtained by the investigator.

During each clinic visit, subjects will be reminded to notify a study team member of the following:

- The occurrence of AEs and SAEs during the respective reporting periods
- Receipt of any concomitant medications during the applicable reporting period
- Plans to move or if contact information changes
- If subject has decided to withdraw from the study
- Change in general health status
- Any other change in status that may affect the subject's participation (e.g., plan to participate in another investigational study)

All deviations from protocol procedures, evaluations, and/or visits must be categorized and documented as they occur. Each deviation must be documented on a Protocol Deviation Form. A cumulative record of all protocol deviations must be maintained on a Protocol Deviation Log. When possible, missed visits and procedures must be rescheduled and performed at the nearest possible time point to the original schedule.

Protocol deviations are to be categorized as follows:

1. Informed consent was not properly obtained.
2. A subject did not meet inclusion/exclusion criteria but was entered into the study.
3. A subject developed withdrawal criteria during the study but was not withdrawn.
4. There was a deviation in randomization, vaccine preparation, or dosing.
5. A protocol-specified visit or procedure was performed out of the allowable window.
6. A protocol-specified visit or procedure was missed (not performed).
7. Other (to be specified in the appropriate documentation)

The signature of the Principal Investigator is required on the Protocol Deviation Form for categories 2 through 5. Certain protocol deviations may also meet the criteria for an Immediately Reportable Event as described in Section 5.12.

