#### **TB Case Definition Endpoint #3**

All individuals who are placed on anti-tuberculosis therapy with the intent of treating tuberculosis, regardless of whether or not they have met the above efficacy endpoint #1 or #2, are considered to have met this exploratory tuberculosis endpoint #3.

The TB endpoint definitions will be applied both to those subjects investigated for TB by the clinical site, and to those subjects who receive a clinical diagnosis of TB disease as part of routine care in other health facilities.

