### 7.3.2 Efficacy of MVA85A/AERAS-485

For the protocol-specified secondary objective of TB disease, subjects will be evaluated for the development of TB disease throughout the study utilizing TB Case Definition Endpoint #1 as the primary disease endpoint assessment. Less stringent TB case definitions, Endpoint #2 and Endpoint #3, will also be evaluated with no adjustment for multiplicity performed; it is acknowledged that the overall Type I error probability is not controlled in the evaluation of these endpoints.

The incidence of TB disease will be calculated as the number of new cases of TB disease in the PP population with a date of diagnosis from 28 days post-Study Day 0 vaccination through the end of study follow-up (as defined for each subject), divided by the total person-time of observation. Person-time observation will be calculated based on subject date of last contact with the study minus the date of Study Day 0 vaccination; sensitivity analyses will be performed to examine time at risk of TB based on INH treatment.

The primary statistical method to be used in the analysis of TB Case Definition Endpoints #1-3 will be vaccine efficacy (VE), estimated as 1-estimated hazard ratio, based on a Cox regression analysis of time to event for each Endpoint utilizing a model containing treatment group, ART status, and study site, performed on the PP population.

Time (months) to initial TB diagnosis for each Endpoint #1, #2 and #3 from Study Day 0 vaccination in each treatment group will be examined using the Kaplan-Meier estimate of the survival function, based on the PP population. Kaplan-Meier curves will be displayed by ART status and treatment group, over time (months) in study (time from Study Day 0 vaccination) to event. Summaries of median time (in months) to initial TB diagnosis and associated two-sided 95% confidence intervals will also be presented for each case definition endpoint. Time to initial diagnosis for each case definition endpoint will be compared using a two-sided log-rank test, stratified by study site and ART status at baseline. As a supportive analysis, the exact binomial (Clopper-Pearson) method will also be used to estimate VE and its corresponding two-sided 95% confidence interval conditional on the total number of events, and corresponding p-value, for each case definition Endpoint. All summaries will be presented by ART status and treatment group for subjects in the PP population.

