Efficacy of MVA85A/AERAS-485 in the prevention of TB disease will be examined for all subjects in the PP population receiving ART at baseline compared to subjects receiving ART at baseline but who receive placebo (secondary objective #3), as described above for secondary objective #1.

In this proof-of-concept study, variables related to HIV status and infection status such as baseline QFN status which may impact development of TB disease may also be included in further stratified Cox proportional hazards regression models, to explore differences between treatment groups in the incidence of TB disease, given proportional hazards assumptions. In addition, the efficacy of MVA85A/AERAS-485 in the prevention of TB disease will be examined for all subjects in the PP population receiving MVA85A/AERAS-485 and isoniazid

preventative therapy at any time during the study following Study Day 0 vaccination compared to subjects receive placebo (secondary objective #4).

Adjustment to time at risk based on start of isoniazid (INH) therapy and examination of cases which occur within 24 months following Study Day 28 (28 days post-Study Day 0 vaccination) will be examined as supportive analyses. Results will be summarized by ART status at baseline, treatment group and study site, as appropriate. Supportive analyses will also be performed based on the ITT population and all randomized subjects' populations. Sensitivity analyses including examination of subjects put on ART during the study and missing data imputations will be explored.

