#### **Post-vaccination:**

- Monitor subject for solicited, unsolicited, and serious adverse events for at least 60 minutes after vaccination (including concomitant medications)
- Obtain 60-minute post-immunization vital signs
- Complete site of injection examination
- Distribute diary cards and review diary card instructions

**Study Visit 1 -** *Allowable window for clinic visit is 7 ±2 days from Study Day 0 (Randomization/initial vaccination).*

- Obtain vital signs
- Review and record any solicited, unsolicited, and serious adverse events (including concomitant medications)
- Monitor subject for clinical observations for signs and symptoms of TB
- Review and record diary card entries for completeness and accuracy
- Complete site of injection examination
- Blood collection for
  - Serum chemistry (GGT, ALT, AST, total bilirubin, ALP, creatinine)
  - Hematology (CBC, differential, platelets)
  - CD4+ lymphocyte count
  - HIV-1 viral load
  - Immunology samples

**Study Visit 2 -** *Allowable window for clinic visit is 28 ±3 days from Study Day 0 (Randomization/initial vaccination).*

- Obtain vital signs
- Review and record any solicited, unsolicited, and serious adverse events (including concomitant medications)
- Monitor subject for clinical observations for signs and symptoms of TB
- Complete site of injection examination
- Blood collection for
  - Serum chemistry (GGT, ALT, AST, total bilirubin, ALP, creatinine)
  - Hematology (CBC, differential, platelets)
  - CD4+ lymphocyte count
  - HIV-1 viral load
  - Immunology samples

**Study Visit 3 -** *Allowable window for clinic visit is 84±7 days from Study Day 0 (Randomization/initial vaccination).*

- Obtain vital signs
- Monitor subject for clinical observations for signs and symptoms of TB
- Review and record any serious adverse events (including concomitant medications)
- Blood collection for
  - CD4+ lymphocyte count

**Study Visit 4 – Booster Vaccination-** *Allowable window for visit is 168 to 252 days from Study Day 0 (Randomization/initial vaccination).*

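### Isoniazid dates are not required outside two 28-day windows, yet Section 7.3.2 analyses time at risk and objective #4 by isoniazid taken throughout the study

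*Protocol*

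**What the plan says.** **Data collection.** Protocol Section 3.6.5 opens with a general rule: "The collection of information on concomitant medications used by subjects following vaccination will coincide with the collection period of adverse events". It then sets the periods:

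- For drugs that treat adverse events: "The collection period for concomitant medications associated with the treatment of adverse events will be 28 days following each vaccination".
- For drugs that treat SAEs, and for "anti-retrovirals for the treatment of HIV will be Study Day 0 through the end of the study".

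Isoniazid is not named. Prophylaxis is an accepted indication on the concomitant medication page, and a start date with a stop date or an ongoing flag is required for each entry.

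The schedules agree with this. Tables 3-1 and 3-2 attach concomitant medications to the solicited AE, AE and SAE rows. In Appendix A, SV3, SV7, the 3-monthly visits and the End-of-Study visit record them only with SAEs. Section 3.6.6 reminds subjects to report "Receipt of any concomitant medications during the applicable reporting period".

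**Analysis.** Section 7.3.2 says that "sensitivity analyses will be performed to examine time at risk of TB based on INH treatment", and lists as supportive: "Adjustment to time at risk based on start of isoniazid (INH) therapy". It also analyses secondary objective #4 among vaccine recipients who took isoniazid at whatever point after the Study Day 0 vaccination, compared with placebo recipients.

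**The concern.** The analysis section relies on a variable that the collection section does not require over most of follow-up. Isoniazid preventive therapy is neither treatment of an SAE nor an antiretroviral, so it falls in no category that runs to end of study. Antiretrovirals had to be named to be collected throughout. That suggests a long-term drug unrelated to an event is not collected unless it is listed.

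A subject whose INH course falls wholly outside the windows has no INH date that the protocol requires. In the time-at-risk analyses that subject stays unexposed and at full risk. As more starts are missed, the INH-adjusted result moves towards the unadjusted one, and agreement between the two would then say little. In the Section 7.3.2 version of objective #4, such subjects drop out of the isoniazid group.

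This gap is not one for the SAP to close, because an SAP cannot analyse dates that sites were never asked to record.

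**Working it through.** The protocol states no figure for this, so there is nothing to reproduce. Two quantities can be derived.

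**Inputs**

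- Recording window: 28 days after each of two vaccinations (Section 3.6.5), so 2 × 28 = 56 days.
- Booster day B: 168 to 252 (Table 2-1).
- Minimum follow-up: 6 months after the last vaccination (Section 2.2), taken as 182 days, so 168 + 182 = 350 to 252 + 182 = 434 days.
- Planned follow-up: about 15 months for the last subject and 36 for the first (Section 7.6). With uniform accrual, which is an assumption, the mean is (15 + 36)/2 = 25.5 months, about 776 days. Thirty-six months is about 1096 days.
- INH course length L: assumed 152 to 183 days (5-6 months). Inclusion criterion 9b gives only a minimum of 5 months, and that for past therapy.

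**(a) Share of person-time inside the windows = 56/F**

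| Follow-up F | Inside | Outside |
|---|---|---|
| 350 days (minimum, booster day 168) | 56/350 = 16.0% | 84.0% |
| 434 days (minimum, booster day 252) | 56/434 = 12.9% | 87.1% |
| 776 days (mean) | 56/776 = 7.2% | 92.8% |
| 1096 days (36 months) | 56/1096 = 5.1% | 94.9% |

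**(b) Share of courses captured, on a generous reading**

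A course counts as captured if any part of it overlaps either window, because its true start date can then be entered. With start times uniform over F, the start days that lead to capture are

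C = 28 + [B + 28 − max(28, B − L)], and the share is C/F.

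| B | L | C | Minimum follow-up (F = B + 182) | Mean follow-up (F = 776) |
|---|---|---|---|---|
| 168 | 152 or 183 | 196 | 196/350 = 56.0% | 25.3% |
| 210 | 152 | 208 | 208/392 = 53.1% | 26.8% |
| 210 | 183 | 238 | 238/392 = 60.7% | 30.7% |
| 252 | 152 | 208 | 208/434 = 47.9% | 26.8% |
| 252 | 183 | 239 | 239/434 = 55.1% | 30.8% |

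The capture share is therefore 48-61% at minimum follow-up and 25-31% at the mean. At 36 months it is 196/1096 = 18% to 239/1096 = 22%. These figures assume that the booster is given and that staff enter prophylaxis during the windows; otherwise capture is lower.

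**(c) Objective #4, the two texts side by side**

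| | Section 2.1 | Section 7.3.2 |
|---|---|---|
| Isoniazid timing | Not stated | On study, after the first vaccination |
| Placebo comparator | Also received isoniazid | Not stated to have received isoniazid |

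The two texts differ in both timing and comparator.

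**The case against.** The strongest case for the plan has five parts.

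1. **There are two windows, and ongoing courses count.** A reader might infer that nothing is recorded after Day 28, or that 93% of INH exposure is lost. The documents support neither. A second window follows the booster, and a course begun earlier but still running can be entered with its start date. The 7% is a share of person-time; it is not a share of courses or subjects. At minimum follow-up about half of courses would be captured. This part stands, and the figures above allow for it.
2. **On-study starts may be few.** Criterion 9 requires test-positive entrants to have completed isoniazid or TB treatment already, and the QuantiFERON and skin tests are repeated only at End of Study. This is fair. However, criterion 9a admits test-negative subjects with no requirement for prior isoniazid, and the documents give no start rate either way.
3. **Objective #4 may not need on-study data.** As worded in Section 2.1 it could be met with isoniazid taken before enrolment, which is established at eligibility and tabulated in Table S1 (144 + 133 = 277 of 649). This stands for Section 2.1. It does not rescue the Section 7.3.2 version, and it exposes the mismatch shown in (c).
4. **Dates may be collected anyway.** The eCRF is not shown, and a medical history is taken at End of Study. So the supportable statement is that the protocol does not require the dates. To say that they were never collected would go beyond the documents.
5. **The main results do not use INH.** Safety is the primary objective, and the main Cox model contains treatment group, ART status and site. This stands and limits the severity.

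A reader might also infer that Endpoint #3, which covers "All individuals who are placed on anti-tuberculosis therapy with the intent of treating tuberculosis", cannot be ascertained. The documents do not support that. Section 3.6.3 provides TB questioning at each visit, work-up, and checks of clinic registers, laboratories and hospitals; Section 7.3.1 applies the endpoints to diagnoses made in routine care; and drugs treating TB that is an SAE are recorded to end of study.

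**Conclusion.** The point holds for isoniazid. The protocol does not require on-study INH start and stop dates outside two 28-day windows, while Section 7.3.2 needs them for its time-at-risk analyses and for objective #4 as analysed there. By person-time, 84% to 95% of follow-up lies outside the windows. By courses, an estimated 69-75% would be missed at mean planned follow-up and 39-52% at minimum follow-up. These figures rest on uniform accrual, uniform start times and an assumed 5-6 month course.

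The number of subjects affected, and hence the effect on estimated vaccine efficacy, cannot be derived from the documents. Because allocation is blinded, misclassification that differs between arms is unlikely. The analyses would still not measure what they set out to measure.

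A secondary objective as analysed, one sensitivity analysis and one supportive analysis are affected. The primary safety objective and the main efficacy model are not. This should be fixed, but it does not undermine the trial.

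**What to change.** 1. In Section 3.6.5, add to the categories recorded from Study Day 0 to end of study: *isoniazid or other TB preventive therapy, with start date, stop date and indication*.
2. In Tables 3-1 and 3-2 and Appendix A, ask about it at SV3, SV4, SV7, the 3-monthly visits and End of Study, covering the whole interval since it was last asked.
3. For subjects already enrolled, back-fill from medical or clinic records. The TB registers in Section 3.6.3 are searched for TB cases and household contacts; nothing says that they list recipients of preventive therapy, so they should not be relied on for this.
4. Reconcile objective #4 between Section 2.1 (and the Study Abstract objectives) and Section 7.3.2 (and the Abstract's analysis text). State whether isoniazid means before enrolment, on study or both, and whether the placebo comparator must also have received it.

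The cost is one eCRF category and its completion instructions, one question at existing visits, some back-filling, and an edit to the objective #4 text. No visit, sample or treatment changes.
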